# *R*otational Thrombo*E*lastometry-guided blood component administration versus standard of care in patients with *C*irrhosis and coagulopathy undergoing *I*nvasive *P*roc*E*dures (RECIPE): study protocol for a randomised controlled trial

**DOI:** 10.1186/s13063-023-07552-1

**Published:** 2023-08-11

**Keywords:** Rotational Thromboelastometry (ROTEM), Viscoelastic tests (VETs), Chronic liver disease, Coagulopathy, Surgery, Cirrhosis, Transfusion, Fresh frozen plasma, Platelets

## Abstract

**Background:**

Patients with cirrhosis often undergo invasive procedures both for management of complications of their advanced liver disease, including treatment for hepatocellular carcinoma, as well as underlying comorbidities. Despite a current understanding that most patients with cirrhosis are in a rebalanced haemostatic state (despite abnormalities in conventional coagulation tests, namely INR and platelet count), patients with cirrhosis are still often given prophylactic blood components based on these conventional parameters, in an effort to reduce procedure-related bleeding. Viscoelastic tests such as Rotational Thromboelastometry (ROTEM) provide a global measurement of haemostasis and have been shown to predict bleeding risk more accurately than conventional coagulation tests, and better guide blood product transfusion in a number of surgical and trauma-related settings. The aim of this study is to assess the utility of a ROTEM-based algorithm to guide prophylactic blood component delivery in patients with cirrhosis undergoing invasive procedures. We hypothesise that ROTEM-based decision-making will lead to a reduction in pre-procedural blood component usage, particularly fresh frozen plasma (FFP), compared with standard of care, whilst maintaining optimal clinical outcomes.

**Methods:**

This is a multi-centre randomised controlled trial comparing ROTEM-guided prophylactic blood component administration to standard of care in patients with cirrhosis and coagulopathy undergoing invasive procedures. The primary efficacy outcome of the trial is the proportion of procedures requiring prophylactic transfusion, with the primary safety outcome being procedure-related bleeding complications. Secondary outcomes include the amount of blood products (FFP, platelets, cryoprecipitate) transfused, transfusion-related side effects, procedure-related complications other than bleeding, hospital length of stay and survival.

**Discussion:**

We anticipate that this project will lead to improved prognostication of patients with cirrhosis, in terms of their peri-procedural bleeding risk. We hope to show that a significant proportion of cirrhotic patients, deemed coagulopathic on the basis of standard coagulation tests such as INR and platelet count, are actually in a haemostatic balance and thus do not require prophylactic blood product, leading to decreased and more efficient blood component use.

**Trial registration:**

RECIPE has been prospectively registered with the Australia and New Zealand Clinical Trials Registry on the 30th April 2019 (ACTRN12619000644167).

## Introduction

### Background and rationale {6a}

The peri-procedural assessment of haemostasis in patients with cirrhosis remains challenging for clinicians.

Historically, cirrhosis had been labelled as a bleeding disorder due to the abnormalities in conventional coagulation tests seen, namely prolonged prothrombin time (PT)/international normalised ratio (INR), and thrombocytopenia. On this basis, traditionally, attempts have been made to correct these parameters with blood component prophylaxis prior to invasive procedures in this patient population [1].

More recently, the concept of “rebalanced haemostasis” in cirrhosis was developed and is now well-established [2]. In addition to the reduction in procoagulants, and thrombocytopenia typically associated with advanced liver disease, there is also a reduction in anticoagulants and an increase in von Willebrand factor and factor VIII [3], leading to a new haemostatic balance. This balance, however, is delicate and can be easily disturbed, predisposing the patient with cirrhosis to both bleeding and thrombotic complications [4].

While patients with cirrhosis do have an increased risk of bleeding complications, aside from portal hypertensive-related events, they experience disproportionately fewer bleeding complications than would be expected by their INR/PT and platelet count values [5]. For most patients, the increased bleeding risk relates to portal hypertension, endothelial dysfunction, bacterial infection, and renal failure rather than defective haemostasis (at least that which is assessed by INR/platelet count) [6–8]. There is now robust evidence that INR/PT do not predict procedure-related bleeding in patients with cirrhosis [9]. The potential impact of thrombocytopenia on procedural bleeding risk remains unclear, with some studies suggesting an increased risk of bleeding in patients with platelet counts less than 50 × 10^9^/L [10], while others do not show a relationship [11–13]. Despite frequent abnormalities in conventional coagulation tests, in most patients with cirrhosis thrombin generation is preserved [14].

Up-to-date international clinical practice guidelines acknowledge the limitations of standard haemostatic tests, particularly prothrombin time/INR, in predicting procedure-related bleeding, and as a consequence, no longer recommend routine pre-procedural blood component prophylaxis based on these parameters [15–17]. Despite this, clinical practice has been slow to change, and patients with cirrhosis are still frequently given blood component products, based on their INR and platelet count abnormalities, in an attempt to reduce peri-procedural bleeding [18]. Although the overall risk of bleeding for patients with cirrhosis undergoing procedures remains low, particularly for low-risk procedures [19–22], there is a subset of patients who do bleed, which is likely to explain the clinician tendency to “correct” standard coagulation tests abnormalities with pre-procedural blood product administration that has continued regardless of guidelines recommending against it. This is despite an acknowledgement that there are significant risks associated with blood component therapy, particularly large-volume products such as FFP, including fluid overload, pulmonary oedema, allergic reactions, and elevation in portal pressure [23, 24].

It is imperative that an improved method of assessing procedure-related bleeding risk in patients with cirrhosis is developed and validated, so that blood products can be efficiently and effectively allocated in this patient population.

In recent years, ‘global’ coagulation tests, such as ThromboElastoGraphy(TEG) and Rotational Thromboelastometry (ROTEM) have been developed. Whereas platelet counts, INR and APTT measure only individual components of the haemostatic system, ROTEM and TEG measure the viscoelastic properties of whole blood to provide a measure of overall haemostasis, from clot formation to clot retraction and fibrinolysis [25]. These point-of-care tests provide quick results and have been used to assess coagulation and guide blood product transfusion in a number of surgical and trauma settings, including liver transplantation [26]. In these settings, these tests predict bleeding and thrombotic risks more accurately than conventional coagulation tests, are associated with a reduction in intra-operative blood loss, decreased rates of blood product usage, and improved mortality [27].

Recently, there has been increasing interest in the use of these viscoelastic tests in liver disease outside of the transplant setting. Two randomised controlled trials have found that using TEG to guide prophylactic blood component transfusion in patients with cirrhosis undergoing invasive procedures resulted in decreased blood product use without affecting bleeding outcomes [28, 29]. Similarly, a randomised controlled trial found that using ROTEM to guide pre-procedural blood product transfusion in the cirrhotic *children* having invasive procedures led to decreased FFP and platelet use, with no significant difference in procedure-related bleeding [30].

We designed this study to assess the utility of a ROTEM-based algorithm to guide prophylactic blood component delivery in *adult* patients with cirrhosis undergoing invasive procedures. We hypothesise that ROTEM-based decision-making will lead to a reduction in pre-procedural blood component usage, particularly FFP, compared with standard of care. We anticipate that there will be no difference in bleeding complications between the two groups.

By attempting to establish the role of ROTEM in assessing coagulation status in patients with chronic liver disease, we hope to improve the identification of those patients with cirrhosis who are and are not at increased bleeding risk, and in turn, improve the identification of those patients who are most likely to benefit from blood component transfusion.

### Objectives [31]

The primary efficacy aim of this study is to compare the proportion of procedures requiring prophylactic transfusion with blood components between ROTEM-based decision-making and standard of care. The primary safety aim is to compare procedure-related bleeding between ROTEM-based decision-making and standard of care management. The secondary objectives of the trial are to compare the following between ROTEM-based decision-making and standard of care: (1) the number of FFP, platelet and cryoprecipitate transfusions given as bleeding-prophylaxis; (2) the occurrence of procedure-related non-bleeding complications (thromboembolism, infection), length of hospital stay and survival; and (3) transfusion-related events.

### Trial design {8}

The RECIPE trial is a randomised controlled trial with a 1:1 allocation to one of two parallel groups (pre-procedural blood component prophylaxis based on a ROTEM algorithm or based on conventional coagulation tests as per standard of care). It is designed as a superiority trial aiming to demonstrate that a ROTEM-based algorithm will lead to a significant reduction in prophylactic blood component usage compared with standard of care. An attempt to blind the patient and proceduralist to the allocated intervention arm will be made. All participants will have otherwise standard peri-procedural care.

## Methods: participants, interventions and outcomes

### Study setting {9}

Participants will be recruited from the inpatient wards and outpatient clinics at several tertiary hospitals and liver-transplant centres across Australia. A list of up-to-date study sites can be obtained through the Australian and New Zealand clinical trials registry.

### Eligibility criteria {10}

#### Inclusion criteria: participants

To be eligible for randomisation, participants must meet the following criteria:Males and females aged 18 years or olderHave liver cirrhosis (of any aetiology), which is biopsy proven or defined by any two or more of the following: Fibroscan reading > 12.5 kPa, APRI (AST to platelet ratio index) score $$\ge$$ 2, ultrasound features of cirrhosis, evidence of portal hypertension on imaging and/or presence of varices, compatible clinical features.Planned for an invasive procedureCoagulopathic based on conventional coagulation tests and considered for pre-procedural blood component prophylaxis as per hospital-specific standard of careAble and willing to provide informed consentAble to speak and understand English

#### Inclusion criteria: invasive procedures

Any procedure (excluding procedures involving the central nervous system) for which an eligible patient would normally be considered for blood component prophylaxis prior to the procedure will be included.

Procedures will be classified into low-risk and high-risk, based on the likelihood of bleeding and the clinical significance of any related bleeding. Classification will be based on that used published in the American Gastroenterology Association guidelines [32]. Low-risk procedures will account for no greater than 25–30% of all procedures.

#### Exclusion criteria

Candidates who meet any of the following criteria are excluded from randomisation:Coagulation disorders (other than those relating to liver disease)Patients on anticoagulant medications (e.g. warfarin, enoxaparin, rivaroxaban, dabigatran, apixaban).Patients on anti-platelet aggregation agents other than aspirin (e.g. clopidogrel, ticagrelor)Patients in whom it is difficult to obtain blood samples due to venous access difficultiesActive malignancy (EXCEPT; hepatocellular carcinoma, cervical carcinoma in situ, treated basal cell or squamous cell skin carcinoma, superficial bladder tumours [Ta, Tis & T1] or any cancer curatively treated >3 years prior to study entry)Patients who have received FFP, platelet transfusion, cryoprecipitate in the week priorPatients with stage 4 or 5 chronic kidney diseasePatients receiving renal replacement therapyPatients with active sepsis

### Who will take informed consent? {26a}

The trial will be explained and informed consent will be obtained by study investigators at the individual study sites. In addition to a verbal explanation, potential participants will be provided with a written patient information and consent form (PICF) and adequate time to read this. The participants will have the opportunity to ask questions.

### Additional consent provisions for collection and use of participant data and biological specimens {26b}

As part of the standard consent form, participants will also be consented for additional blood samples to be stored and used for further coagulation testing in the future.

## Interventions

### Explanation for the choice of comparators {6b}

The RECIPE trial is designed to compare ROTEM-guided blood component prophylaxis with standard of care blood component prophylaxis in patients with cirrhosis having invasive procedures.

At the time of our protocol development, there had been no previously published ROTEM decision-making algorithm for patients with cirrhosis having invasive procedures. The ROTEM-based algorithm we have developed is based on those that have been published for use in other settings (liver transplant and cardiothoracic surgery [26]) and then modified by an expert panel of haematologists (co-investigators HN and CH).

For our standard of care arm, the INR and platelet cut-offs used to guide blood component prophylaxis have not specifically been defined and instead will be at the discretion of the individual study sites and proceduralists. This decision was made on the basis of previous work published by our team which found significant heterogeneity in routine prophylactic transfusion practices across Australian institutions for different procedures and different trigger INR and platelet cut-offs [18].

### Intervention description {11a}

All participants will have baseline pathology including standard coagulation testing and a ROTEM analysis.

ROTEM analysis will be performed by one of the investigators using the ROTEM-sigma device located at the study site, within 4 h of the participant’s blood draw. The ROTEM-sigma performs all analyses on citrated whole blood and will be run according to the manufacturer’s instructions. Each blood sample will be tested using four ROTEM assays with different reagents provided by the manufacturer: each of these assays evaluates overall clot formation and strength. The EXTEM evaluates clot formation mimicking the conventional extrinsic pathway, INTEM evaluates clot formation mimicking the conventional intrinsic pathway, FIBTEM evaluates the contribution of fibrinogen to clot formation, and APTEM which evaluates any antifibrinolytic effect. All other laboratory tests will be run by the Hospital pathology laboratories at the study sites.

#### Standard of care intervention

Participants assigned to the standard of care intervention will receive prophylactic blood components (FFP, platelet transfusion, cryoprecipitate) based on INR and platelet count prior to their procedure. The INR and platelet cut-offs used to determine whether blood product is required, the type and dose, will be based on standard of care at the hospital where the procedure is taking place, and as such may vary between sites and procedures. The required blood products are ordered and administered to the patient immediately prior to the procedure.

#### ROTEM-based intervention

For participants assigned to the ROTEM-based decision-making arm, the following ROTEM parameters will be used to determine whether pre-procedural blood product should be given (see Fig. 1 below):Clotting time using EXTEM (CT_EX_)Amplitude at 5 min using EXTEM (A5_EX_)Amplitude at 5 min using FIBTEM (A5_FIB_)

**Fig. 1 Fig1:**
[figure not shown]
ROTEM algorithm for prophylactic blood component

If it is determined that blood products are required, these are ordered and administered to the patient immediately prior to the procedure.

Patients in both the ROTEM and standard of care arms will have the same peri-operative management aside from that related to the method used to assign prophylactic blood component.

### Criteria for discontinuing or modifying allocated interventions {11b}

All participants can decide to withdraw from the study for any reason and at any time during the study. If it is before the time of intervention, prophylaxis will be guided by standard of care. The investigator can also decide to withdraw a patient from the study if he/she considers it as necessary (e.g. non-respect of at least one of the selection criteria known after inclusion, or for patient safety). When a patient withdraws from the study, all collected data up until the time of withdrawal will be analysed unless the participant requests deletion of their data.

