## Assignment of interventions: blinding

### Who will be blinded {17a}

Participants will be blinded to the results of their ROTEM analysis and will not be told whether they are assigned to the ROTEM-based arm or standard of care. However, it is possible that those participants who end up not requiring prophylactic blood product transfusion may deduce that they have been randomised to ROTEM-based decision-making. The proceduralist will also be blinded to the allocation. The study investigator and treating team are not able to be blinded, as it is necessary for these staff to order and administer the blood products. The person performing the randomisation will be blinded to the result of the ROTEM analysis. Given the hard outcomes of the study, we do not think the lack of blinding of the treating clinicians will greatly bias the results.

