### Plans to promote participant retention and complete follow-up {18b}

The RECIPE study follow-up duration is only 28 days. For participants who are discharged from the hospital before the day 7 or day 28 follow-up assessments, these will be conducted over the telephone to maximise participant retention and follow-up. For participants who deviate from intervention protocols, an attempt will still be made to collect all outcome data.

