## Statistical methods

### Statistical methods for primary and secondary outcomes {20a}

All statistical analyses will be performed using STATA.

The primary efficacy outcome will be an intention-to-treat analysis, comparing the proportion of procedures requiring prophylactic blood component transfusion between the two randomised groups. The primary safety outcome will be a per-protocol analysis comparing the percentage of procedures associated with a procedure-related bleeding complication between the two groups. The secondary outcomes will either be analysed as intention-to-treat analyses (for survival), modified intention-to-treat (comparing specific blood products or transfusion-related side effects) and per protocol analyses (for procedure-related complications other than bleeding and hospital length of stay). The primary outcomes and secondary outcomes comparing proportions or percentages will be compared using chi-squared or Fisher’s exact tests. The secondary outcomes examining continuous variables will be compared using the Mann–Whitney test. A *p*-value less than 0.05 is considered statistically significant in a two-sided test.

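### Withdrawal by an unblinded investigator is not separated from leaving follow-up, so the intention-to-treat efficacy and day-28 survival analyses can lose outcomes informatively

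*Protocol article*

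**What the plan says.** Section {11b} of the Protocol article first allows participants to leave at any time and adds: "If it is before the time of intervention, prophylaxis will be guided by standard of care". It then turns to the investigator: "The investigator can also decide to withdraw a patient from the study if he/she considers it as necessary". The examples given are "non-respect of at least one of the selection criteria known after inclusion, or for patient safety". The next sentence is the only rule on data: "When a patient withdraws from the study, all collected data up until the time of withdrawal will be analysed", unless the participant asks for deletion.

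Section {18b} has a separate rule for another group: "For participants who deviate from intervention protocols, an attempt will still be made to collect all outcome data". It does not mention withdrawn participants.

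On blinding, section {17a} says: "The study investigator and treating team are not able to be blinded".

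Section {20a} makes the primary efficacy comparison and survival intention-to-treat. For bleeding it says: "The primary safety outcome will be a per-protocol analysis". Section {12} assesses survival at day 28. Section {20c} expects no missing data, while section {14} allows 10% for drop-outs and missing data.

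**The concern.** Three different events share one label: a participant's withdrawal of consent, an investigator's removal of a patient for safety, and an eligibility failure found after inclusion. Only the first gives a reason to stop collecting outcomes. For the other two the participant may be quite willing to be followed, and the outcomes are still obtainable.

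A safety removal is made after randomisation, by someone who knows the arm, about a patient who has caused worry. Loss of that kind may well be related to both outcome and allocation. Intention-to-treat analysis protects against it only if the outcomes exist. No later choice of analysis set can bring back outcomes that were never collected, so this is a matter for the protocol and cannot be left to an analysis plan.

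**Working it through.** **1. The passages side by side.** Suppose a site abandons the allocated strategy for a randomised patient because it looks unsafe.

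- Recorded as a deviation: section {18b} applies, and all outcomes are sought to day 28.
- Recorded as a withdrawal: section {11b} applies, and the analysed data end at that moment.

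Nothing in the document says which label to use. The outcomes at risk depend on timing:

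- Withdrawal before any product is given: the primary efficacy outcome (product given before the procedure), bleeding, complications and survival all fall after the cut.
- Withdrawal after the procedure but before day 28: efficacy is already known; later bleeding, complications and survival are lost.

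**2. The plan's own allowance.** Section {14} gives 56 in total (28 per arm), with 90% power, 5% alpha and 10% loss. The control rate is not stated. Assuming 100% versus 70%, two-sided, with unpooled variance:

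n = (p1q1 + p2q2)(z_a + z_b)² / d² = (0 + 0.70 × 0.30)(1.960 + 1.282)² / 0.30² = 24.5, rounded up to 25 per arm.

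25 / 0.9 = 27.8, rounded up to 28 per arm, so 56. The figure reproduces and is not in dispute. It shows that the plan allows for 28 − 25 = 3 lost per arm, from all causes.

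**3. What missing outcomes do to an intention-to-treat proportion.** With w of 28 outcomes missing in one arm and x events seen, the proportion by randomised arm lies between x/28 and (x + w)/28. The width is w/28:

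| w | width |
|---|---|
| 1 | 3.6 points |
| 2 | 7.1 points |
| 3 | 10.7 points |

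For efficacy, 10.7 points is about a third of the 30-point difference assumed in step 2 (10.7/30 = 0.36). For survival, no deaths among 25 followed would be compatible with anything from 0/28 to 3/28 (10.7%). These are bounds, not estimates of bias. How much of the 10% would be investigator withdrawals is not known.

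**4. Bleeding.** Assume 3 ROTEM-arm patients are withdrawn before the procedure, 1 of them bleeds, and 2 of the other 25 bleed.

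| Analysis | Outcomes not collected | Outcomes collected |
|---|---|---|
| Per protocol (withdrawn patients outside the set) | 2/25 = 8.0% | 2/25 = 8.0% |
| By randomised arm | between 2/28 = 7.1% and 5/28 = 17.9% | 3/28 = 10.7% |

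The planned per-protocol result is the same in both columns. Only the analysis by randomised arm gains from follow-up.

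In a more extreme assumption all 3 withdrawn patients bleed, no other ROTEM patient does, and standard of care has 0/28. The comparison by randomised arm is then 3/28 versus 0/28 (Fisher p = 0.24), against 0/25 versus 0/28 (p = 1.0) without those patients. Neither is significant, so what is at stake is the estimated rate, not a significance verdict.

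**The case against.** **The text does not say that collection stops.** Correct. The sentence in {11b} can be read as a retention rule: what has been collected is kept. A reader might infer an explicit order to end follow-up, but the document contains none. It remains the natural reading, because a cut-off is named and no rule provides for later data.

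**The sentence may cover only participants who withdraw themselves.** Its opening words and its reference to deletion fit that reading. But it directly follows the sentence on investigator withdrawal. If it does not apply there, investigator-withdrawn patients have no data rule at all, and the same clarification is needed.

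**The standard-of-care sentence.** A reader might take it to cover safety removals by the investigator. It follows the sentence on participants' own withdrawal and precedes the investigator sentence, so the document does not support that extension.

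**Section {18b} already covers abandoning the strategy.** It does if the act is called a deviation, but that choice of label is the gap.

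**Bleeding is analysed per protocol.** A reader might infer that the rule in {11b} lowers the reported bleeding rate. It probably does not: patients not managed by their allocated strategy would ordinarily fall outside a per-protocol set even with full follow-up. This objection stands for the planned bleeding analysis, but not for efficacy or survival.

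**The window is short, and the article is condensed.** Sampling is within 24 h of the procedure (72 h for stable outpatients) and randomisation follows, so withdrawals before the procedure should be few. The full protocol may define terms more finely. Both points limit the likely size. Neither changes the fact that the article states a data rule that does not distinguish these cases.

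**Conclusion.** The point holds as a defect in how {11b} and {18b} fit together. On the natural reading of {11b}, an unblinded investigator's decision can end the analysed data of a willing participant, and whether follow-up is kept depends on the label. The intention-to-treat analyses of primary efficacy and day-28 survival can be left informatively incomplete, and bleeding cannot be compared by randomised arm for those patients.

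The size is unknown. Each lost outcome leaves 3.6 percentage points of its arm's proportion undetermined, and 3 lost leave 10.7. That upper figure assumes the whole 10% allowance is used up by such withdrawals in one arm. The direction is also unknown. It is plausible that safety removals would be more common where product is withheld, and a reader might infer a bias in favour of ROTEM. The document gives nothing to show it.

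**What to change.** Amend section {11b} to say that:

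- an investigator decision, whether for safety or because a selection criterion is found unmet after randomisation, ends only the allocated strategy;
- the participant still has the day 0, 7 and 28 assessments and stays in the randomised arm for the intention-to-treat analyses;
- data collection ends only when the participant withdraws consent for follow-up;
- the reason for and time of each such decision are recorded and reported by arm.

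Align {18b} so that its commitment names these participants. In {20a}, report bleeding by randomised arm alongside the per-protocol analysis; otherwise the additional bleeding data would go unused. No treatment rule changes.

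The cost is a few more telephone or record checks of the kind already planned, plus the data safety monitoring board and ethics approval that section {25} requires for any modification. Recruitment began in February 2021, so for any participant already withdrawn by an investigator, outcomes should be sought from records where consent allows.
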